### Adverse Event Severity – Definition

The severity of adverse events will be graded on a three point scale:

**Mild**: discomfort noted, but no disruption to normal daily activities.

**Moderate**: discomfort sufficient to reduce or affect normal daily activities.

**Severe**: inability to work or perform normal daily activities.

**Potentially Life Threatening:** participant at immediate risk of death

### Serious Adverse Events

According to the ICH E6 Good Clinical Practice Guidelines [3], a Serious Adverse Event (SAE) is defined as a medical event that occurs at any dose of the investigational product and results in any of the following:

• Death

• Life-threatening adverse drug experience (participant at immediate risk of death)

• Requires prolonged inpatient hospitalization

• Results in persistent or significant disability/incapacity

• Results in congenital anomaly or birth defect

• Other medical events that do not result in death, are life-threatening, or require hospitalization may also be listed as a SAE when, based upon appropriate medical judgment, they may jeopardize the participant and may require medical and surgical intervention to prevent one of the outcomes listed in this definition. Examples of such medical events include allergic bronchospasm requiring intensive treatment in an emergency room or at home, blood dyscrasias or convulsions that do not result in inpatient hospitalization, or the development of drug dependency or drug abuse.

If any AE is classified as a serious adverse event by the CI or the co-investigator, or if it meets the criteria for a SAE, the occurrence must be:

• recorded on the appropriate serious adverse event case report form, source documents i.e. medical records and SAE report forms for vaccines;

• followed through resolution by a study physician;

• reviewed by a study physician.

### Procedures to be Followed in the Event of Abnormal Laboratory Test Values or Abnormal Clinical Findings

Safety laboratory tests will be performed at the follow-up visits scheduled at 28 days after each vaccination (days 28 and 84) and days 180, 266 and 350. See section 8.2.1 for list of safety laboratory tests. Toxicity tables are provided in Appendix B of this protocol and grade the severity of the laboratory abnormality as mild, moderate or severe. Laboratory abnormalities will be assessed as associated or not associated as described in section 9.2.1.

## Reporting Procedures

The CI is responsible for reporting all AEs that are observed or reported during the study, regardless of their relationship to the study product. Safety reporting regulations are defined in the ICH GCP.

### Serious Adverse Events

All Serious Adverse Events as defined in section 9.2.2 above will be reported immediately to QIMR as the TGA sponsor as per relevant QIMR standard operating procedures.

Within 24 hours the CI or the study co-investigator becoming aware of an SAE should:

- - Notify the QIMR Regulatory Affairs and the independent medical monitor of the SAE occurrence
  - Complete the initial SAE report by completing the details on the QIMR SAE Report
  - Fax the completed initial SAE report to the:

**QIMR Regulatory Affairs Office,**

**[name],**

**[name]**

- - The SAE report should be submitted to the QIMR-HREC by the QIMR PI via the E-Form system.

Within 14 days of onset of the SAE –

- The PI will complete the follow-up SAE report by filling in SAE follow-up details on the QIMR SAE Report and entering “Follow-up” on the “Report Type” field. The reporting investigator should sign and date the report.
- The completed Follow-up SAE report should be faxed to the:

**QIMR Regulatory Affairs Office,**

**[name],**

**[name].**

- The SAE report should be submitted to the QIMR-HREC by the QIMR PI via the E-Form system.

Other supporting documents of the event may be requested by the QIMR Regulatory Affairs or the ISM and will be provided as soon as possible.

Summary reports for the occurrence and the follow up of all SAE observed will be sent to the ISM on a monthly basis for a review and be incorporated into a report for SMC review. Once the reports have been reviewed by the ISM, copies from the reports will be faxed back to the clinical site to be filed with the source documents and the medical records.

### Regulatory Requirements

Events both serious and unexpected that are associated with the administration of the vaccines will be reported by the TGA sponsor (QIMR) or designees to the TGA regulatory authorities.

The reviewing and reporting to TGA of all serious and unexpected adverse reactions will comply with relevant QIMR policy and TGA requirements as outlined in the “Therapeutic Goods Administration (TGA), Access to Unapproved Therapeutic Goods - Clinical Trials in Australia” document and ”The Australian Clinical Trial Handbook”.

Following the notification from the CI or the co-investigator, the sponsor for TGA (QIMR), will notify TGA for occurrence of SAE within the required timelines:

• Fatal or life-threatening events will be reported to TGA within 7 calendar days with a follow up report to be submitted within 8 additional calendar days.

• A full report for all other serious and unexpected events should be submitted no later than 15 calendar days after first knowledge by the sponsor.

• All other reactions and adverse events will be reported to the relevant ethics committees and TGA at least annually in a summary format.

The Independent Safety Monitor will have direct contact with the CI who is responsible for QIMR reporting to the TGA in accordance with relevant QIMR policy.

### Reporting of Pregnancy

The occurrence of pregnancy at any stage during the trial will be recorded in the case report form. Any further administration of the study product will be discontinued. With the participant’s permission, she will be followed up in accordance to the clinical site work instructions for follow up pregnancies. The participant will be asked to continue the scheduled follow up visits until the following dose (if applicable) for safety evaluation for doses already received and then at the end of the study. Additionally, the pregnancy outcome will be recorded in the CRF.

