A Memory Aid (MA) will be provided to participants to record their oral temperature, solicited and unsolicited symptoms, adverse events and concomitant medications. Each participant will be asked to record in memory aids the occurrence of any symptoms at the injection site (such as pain, tenderness, pruritis, erythema and induration) and systemic reactions such as fever, anorexia, nausea, malaise, myalgia, arthralgia and headache. Participants will also be asked to record any changes in urine that might suggest haematuria (blood-tinged or cola-coloured urine) and cutaneous abnormalities (rash or subcutaneous nodules). Information will be recorded daily for 7 days after each injection. Study personnel will review the information on the Memory Aid with the participant via phone calls (day 2 and 8 days after injection) to elicit as much information as possible about any reported symptoms. Based on this information, study staff will use his/her clinical judgment to assess the event and its severity and record the data on the Reactogenicity Record. Study staff will use the Reactogenicity Record to enter information into the database. The Memory Aid will not be collected from the participants.

All participants will be encouraged to contact clinical investigators or to visit the clinical site if they observe any grade 3 AE of the above mentioned reactions following each immunization.(see Appendix B), or if they have any concern. Adverse events and serious adverse events will also be reported at clinic visits throughout the study period.

Each participant will be required to visit the investigation site at the allocated days. Targeted physical examinations including cardiac auscultation by physician will be performed on day 28 after each vaccination and at follow-up visits on days 180, 266 and 350. Additional cardiac evaluation will include an electrocardiogram and transthoracic echocardiogram at day 28 following each injection and at the final follow-up visit on day 350. All study visits will be within the acceptable windows shown on Appendix A.

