### Reasons for Withdrawal

A participant will not receive further study product if unexpected serious clinical adverse event (SAE), an illness or medical condition, or a situation occurs such that in opinion of the Clinical Investigator, continued receipt of vaccinations would not be in the best interest of that person. Participants may voluntarily withdraw from receipt of future product administration and/or follow-up at any time.

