### Handling of Withdrawals

If the participant is withdrawn from the study procedures or follow-up for any reason, with the participant’s permission, medical care will be provided for any SAEs that might have had occurred during the individual participation in the study until the symptoms of any SAEs are resolved and the participant’s condition becomes stable. If withdrawal from further product administration occurs, if willing the participant will be asked to continue the scheduled evaluations and to complete the early termination evaluation as described in section 7.6.

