**Day 56 ± 5 (Day of Dose 2)**

1. Ensure that an approval has been granted from SMC to proceed with the second study product administration.

2. Review inclusion/exclusion criteria.

3. Review medical history for any change in status from last study visit.

4. Review any acute complaints/adverse events/serious adverse events.

5. Review concomitant medications. If the participant has received an antibiotic treatment within 14 days prior to this administration, at discretion of the CI the participant may be withdrawn from the study or the administration of the second dose rescheduled within the allowed window for administration of the dose.

6. Record baseline symptoms and vital signs. If the participant is febrile (temperature >38°C [>100.4F] or has an acute illness, the study product administration must be rescheduled within the allowed window for administration of the dose.

7. Obtain a throat swab and conduct a rapid antigen test for group A streptococci.

8. Obtain a urine sample from all female participants for -HCG testing. Ensure that the testing is negative before study product administration.

9. Perform breath alcohol test and urine drug screen.

10. Collect urine for urinalysis and blood for hematology, biochemistry and serology including, ASOT, α-DNase B and detection of α-J8 peptide vaccine specific antibodies and blood sample for quantitative cellular response as well as serum samples for α-DT antibodies and safety serum storage (refer to appendix D for tests required and blood volumes).

11. Targeted physical examination including cardiac auscultation. Particular attention to any elicited symptoms and signs consistent with rheumatic fever i.e. rash, arthalgia/arthritis (joint pain/swelling), renal angle tenderness and cardiovascular examination and movement disorder.

12. Administer the study product in the alternate arm from previous dose.

13. Observe for at least 30 minutes after study product administration to evaluate for immediate adverse reactions. Repeat vital signs after approximately of 30 minutes after study product administration, or at least prior to discharge. Record any immediate injection site reaction or systemic reactions if they occur.

14. Educate the participant during the post-study product administration waiting period on proper use of the thermometers and injection site reaction measurement aid. Discuss the signs and symptoms of potential adverse events (AEs).

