• Vital signs will be collected and acute complaints examined by clinical personnel prior to each study product administration and at all scheduled clinic visits. Each participant will be subject to a physical examination by a physician at screening to evaluate the general health status of the participant. This will include body weight, vital signs (blood pressure, temperature, heart rate and respiratory rate), an examination of vital organs and cardiac auscultation. Targeted (abbreviated) physical examination including cardiac auscultation will also be performed prior to study product administration of each injection and at all scheduled study visits (Appendix A). Exam will include particular attention to any elicited symptoms and signs consistent with any adverse events. Any deviations from normal will be reported to the study physician for a review. All deviations from normal detected by physical examination will be graded as 1 (mild), 2 (moderate), 3 (severe) and 4 (life threatening) (see Appendix B).

• Transthoracic echocardiography (ECHO) and electrocardiogram (ECG) tests will be performed for each participant in this study at screening, 28 days after each injection and at the final visit on day 350 by a technician blinded to the type of treatment that the participants are receiving. A single echo technician and a single cardiologist have been recruited to perform and interpret all ECHO findings. The technician will be located at the clinical site and the cardiologist reading the findings will be located in the hospital which is physically separated from the clinical site where study activities will be conducted. There will be no discussion regarding the clinical trial between the trial personnel and the hospital personnel. Echocardiograms will be reviewed for any abnormalities by the study cardiologist who will be also blinded to type of treatment that the participants are receiving. If any findings are identified as abnormal a second cardiologist will be asked to independently review the test results and report on the findings. If an abnormal ECHO/ECG is confirmed, it will be reported to the Independent Safety Monitor and Safety Monitoring Committee to determine whether it meets halting rules. Any change in degree of mitral regurgitation with EROA 10-19mm2 but a change of <10mm2 from baseline will be followed on a monthly basis with echocardiogram on a monthly basis until stable (Appendix H).

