## Type and Duration of Follow-up of Subjects after Adverse Events

All AEs will be followed up until resolved or stabilized. The medical care provided will be decided by the CI and clinical personnel involved in the study to provide the best outcome and recovery for the study participant. In general, all AEs will be recorded at each of the scheduled interim visits until AE are resolved or stabilized.

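### For a pregnancy found between the two doses, section 9.3.3 naturally read requests no scheduled trial visit between Day 56 and Day 350, a thinner safety follow-up than other participants off product are asked for

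*Protocol*

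**What the plan says.** Section 9.3.3 (Reporting of Pregnancy) has four parts. Further product is stopped. With her permission, the participant is followed under the site's own work instructions for pregnancies. She is asked to keep attending scheduled visits "until the following dose (if applicable) for safety evaluation for doses already received and then at the end of the study". The pregnancy outcome is recorded.

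Other participants who stop product are treated differently:

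- Section 5.3.5 (Handling of Withdrawals): "If withdrawal from further product administration occurs, if willing the participant will be asked to continue the scheduled evaluations". This is not confined to voluntary withdrawal. Section 5.3.4, just before it, includes stops decided by the clinical investigator: "A participant will not receive further study product if unexpected serious clinical adverse event (SAE), an illness or medical condition, or a situation occurs".
- Section 6.4 (Concomitant Medications/Treatments): a participant stopped because of an excluded medication is encouraged to stay on the visit schedule, with no cut-off. The stated purpose is to follow the safety of doses already given, which is also the purpose stated in 9.3.3.
- Section 7.6 (Early Termination Visit): participants who withdraw from further product are encouraged to keep to the visit schedule.

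Section 9.3.3 cites none of these sections, and none of them cites it.

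Section 9.2.3 places the safety laboratory tests "at 28 days after each vaccination (days 28 and 84) and days 180, 266 and 350". Section 4 says that targeted examinations with cardiac auscultation "will be performed on day 28 after each vaccination and at follow-up visits on days 180, 266 and 350". Section 8.1 says that ECG and echocardiogram "will be performed for each participant in this study at screening, 28 days after each injection and at the final visit on day 350".

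**The concern.** Section 7.3 requires a urine pregnancy test at the Day 56 visit: "Ensure that the testing is negative before study product administration". The visit lists in section 7 contain no pregnancy test after that. The last scheduled test therefore falls exactly where the wording of 9.3.3 gives the least follow-up: after a positive result on Day 56, the next scheduled trial visit requested is Day 350.

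Section 3.2.1 names changes in auscultation and in laboratory values among the safety parameters of the primary outcome. Section 2.3.1 names an autoimmune response with pathology of the rheumatic fever or rheumatic heart disease type as a possible risk. The examinations at Days 180 and 266 are directed at signs of rheumatic fever. A participant who has had one dose of vaccine carries some exposure to that risk, yet would be asked for neither visit. A change in laboratory values or auscultation without symptoms would not surface through spontaneous adverse event reporting. The antibody samples due at the same visits would also be missed, although for a one-dose participant they carry less weight.

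**Working it through.** The protocol gives no figure of its own on this point, so the check sets the pregnancy rule against the visit schedule in section 7.

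**Inputs (section 7):** Dose 2 at Day 56 ± 5; clinic visits at Day 84 ± 7, Day 180 ± 14, Day 266 ± 14 and Day 350 ± 14. The pregnancy is found after Dose 1 and no later than the Day 56 pre-dose test, and the Day 56 visit is counted as attended.

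| Visit after Day 56 | Safety content | 9.3.3, natural reading | Schedule continued |
| --- | --- | --- | --- |
| Day 84 | examination, laboratory tests, ECG, echocardiogram | not requested | unclear without Dose 2 |
| Day 180 | examination, laboratory tests | not requested | requested |
| Day 266 | examination, laboratory tests | not requested | requested |
| Day 350 | examination, laboratory tests, ECG, echocardiogram | requested | requested |

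**Visits not requested.** Leaving Day 84 aside, 2 of 3 (Days 180 and 266). Counting Day 84, 3 of 4. Day 84 is kept apart because sections 7.3 and 9.2.3 define it as 28 days after the second vaccination, so what is due there without a second dose is not clear.

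**Gap under 9.3.3.**
- Nominal: 350 − 56 = 294 days.
- Shortest with windows: (350 − 14) − (56 + 5) = 336 − 61 = 275 days.
- Longest with windows: (350 + 14) − (56 − 5) = 364 − 51 = 313 days.

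**Longest gap if the schedule continues and Day 84 is kept.** The gaps are 84 − 56 = 28, 180 − 84 = 96, 266 − 180 = 86 and 350 − 266 = 84. The longest is 96 days, with windows (180 − 14) − (84 + 7) = 75 to (180 + 14) − (84 − 7) = 117.

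**Longest gap if the schedule continues and Day 84 lapses.** The gaps are 180 − 56 = 124, then 86 and 84. The longest is 124 days, with windows (180 − 14) − (56 + 5) = 105 to (180 + 14) − (56 − 5) = 143.

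**What is kept under either rule.** The reactogenicity calls after Dose 1, the Day 28 laboratory tests, examination, ECG and echocardiogram, and the full Day 350 visit.

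**The case against.** The strongest case on the other side is that 9.3.3 is the only text on a pregnancy that occurs after dosing, and that it is complete in itself. A specific rule beside a general one is not a contradiction. A lighter interim schedule for a pregnant participant who has had one dose can be defended: the per-dose safety data through Day 28, which section 9.6 gives the Safety Monitoring Committee to review, are kept, and Day 350 repeats the cardiac work-up. This stands. A reader might infer that 9.3.3 and 5.3.5 conflict outright, but the text does not support that.

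Section 5.3.5 is also not a clean benchmark. It refers to the scheduled evaluations without saying all of them, and the same sentence adds the early termination evaluation, which 7.6 intends for people who do not wish to continue visits. This weakens 5.3.5 taken alone. Sections 6.4 and 7.6 still point the same way, though their triggers differ from pregnancy.

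The words in parentheses in 9.3.3 leave a second reading. If product has been stopped, no following dose applies, and visits might simply run on to the end. That is possible, but it makes the separate mention of the end of the study redundant, so the shorter schedule is the more natural reading.

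The section 7.4 headings for Days 180 and 266 also count weeks from the last injection. Sections 4 and 9.2.3 nevertheless give these visits as plain study days, so they do not lapse in the way Day 84 might.

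Finally, other follow-up goes on. Site pregnancy follow-up continues under instructions that are not shown, and section 9.4 says "All AEs will be followed up until resolved or stabilized". Appendix A is not shown either. One cannot conclude that she would be without medical contact, only that the protocol does not say that this contact includes the scheduled measurements.

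**Conclusion.** The point holds as a weakness in the follow-up rule, at a low level of importance. For a pregnancy found between the doses, the natural reading of 9.3.3 leaves Days 180 and 266 unrequested, and arguably Day 84, so that 294 days (275 to 313) pass without a scheduled trial visit. Continuing the schedule would hold the longest gap to 96 or 124 days, depending on Day 84. The protocol gives no reason why the same stated purpose leads to a shorter schedule here than in 6.4.

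Two further inferences are not supported. Loss of the Day 84 ECG and echocardiogram is only arguable, since they are tied to an injection she would not have received. For a pregnancy after Dose 2 the wording is ambiguous, and no loss can be claimed.

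The conclusion assumes the natural reading of 9.3.3 and that the unseen site instructions do not reproduce the scheduled measurements. Attendance is voluntary under every rule. The number affected cannot be derived from the protocol and may be zero, because section 5.1 requires women to agree not to become pregnant for the first 180 days and to use contraception if sexually active. The effect stays within that participant's record. No estimate, sample size or halting rule changes.

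**What to change.** In section 9.3.3, replace the visit instruction with one sentence: after product is stopped for pregnancy, the participant is asked, if willing, to continue the scheduled safety visits through Day 350, in addition to pregnancy follow-up and recording of the outcome. Allow individual procedures to be omitted on clinical judgment or at her wish. The same sentence should say whether the Day 84 visit is held when Dose 2 was not given.

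The visits already exist in the schedule, so nothing new has to be set up. The downside is a small visit burden for a pregnant participant, which she may decline. Merely adding a cross-reference or a pregnancy exception to 5.3.5 would tidy the text but would not bring back the examinations and laboratory tests.
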